## 2. Materials and Methods

### 2.1. Study Design and Setting 

This is an open label RCT being performed at a single level I trauma center: St. Anthony Hospital in Lakewood, CO. This RCT was designed primarily to determine whether adjunctive dronabinol reduces opioid consumption compared to control. The study was designed with a stratified randomization by baseline marijuana use, which is intended to determine whether the treatment effect of dronabinol is greater in chronic marijuana users compared to recreational or non-marijuana users. This stratified randomization design was incorporated based on the gestalt that cannabis-based medication has a greater benefit for marijuana users.

There is a 48-hour screening/randomization window, a 48-hour treatment window, and a total participation period extending through the acute hospitalization. A description of the clinical trial is posted at ClinicalTrials.gov.

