### 2.2. Study Subjects

Patients are being recruited from the participating trauma center to which they are acutely presenting. A total of 122 adult trauma patients will be randomized 1:1 across 2 study arms: adjunctive dronabinol or control (systemic analgesics only), as shown in Figure 1. 

Patients should fulfill all of the following inclusion criteria:Male or female, 18 years to 65 years old (inclusive).Diagnosis of traumatic injury based on ICD10 diagnosis of S00-T14, which covers injuries to any region of the body.Moderately high initial morphine equivalent use ≥50 mg within a 24-hour window during the screening period. Opioids will be converted to morphine equivalents (mg) using an Equianalgesic conversion chart, Table 1 [11].Willing to disclose current marijuana status (current user (habitual/chronic or recreational), former user, never user).

Patients fulfilling one or more of the following criteria may not be enrolled in the study:Patients on a pain management agreementPatients who are nil per os (NPO) at the time of randomization or are expected to be NPO within the next 48 h, with the exception for a brief NPO period for surgical proceduresPatients who have received or are expected to receive neuraxial/locoregional blocks for pain within the next 48 hoursPatients with a known allergy or previous hypersensitivity reaction to dronabinol or sesame oilPatients prescribed dronabinol between arrival and prior to randomizationPregnancy or breast feedingIncarceration (presumed; patients are not arraigned until after hospital discharge).

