### 2.3. Study Visits

The following procedures will be performed at screening, within 48 h of hospital admission: ensure patient meets inclusion and exclusion criteria; record 24-hour total morphine equivalents; record habitual marijuana usage; obtain informed consent via patient or proxy. 

Once patients are confirmed to meet all criteria and have signed an informed consent, they will be randomized 1:1 across the two study arms (dronabinol or control, Figure 1). The following procedures will be performed during randomization: randomize the patient using the Microsoft Excel blinded randomization schema; record pain using the patient self-reported pain numeric rating scale (NRS, 0–10 scale). 

The following procedures will be performed during the acute hospitalization, post-randomization: if randomized to the dronabinol arm, administer the first dose within the first scheduled dose window and within 12 h of randomization. Record all doses received, including date, time and dose; record all opioid and non-opioid systemic analgesics received, including route/dose/frequency; record all non-analgesic concomitant medications; record pain NRS scores at the following time points: once admitted in hospital bed, preoperatively in the OR prior to anesthesia, one hour post operatively; record all analgesic complications; record all documented drug use from patient self-report and urine drug screening results. Detailed information on the regularity of marijuana use will also be recorded. 

The following procedures will be performed at hospital discharge: record discharge pain NRS score; record discharge location; re-consent, if necessary. 

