### 2.6. Outcome Measures

Patients will be followed to hospital discharge for outcomes of morphine equivalent use, length of stay, pain NRS scores, hospital complications, and analgesic complications. 

The primary outcome is morphine equivalents. All opioids consumed will be converted to morphine equivalents, as shown in Figure 1 [11]. The clinical effects of treatment arm on morphine equivalents will be evaluated at 48 h after randomization. 

Secondary outcomes include the following:Morphine equivalents: overall (hospital admission through discharge or death)Non-opioid analgesics: overall doses received (admission through acute hospitalization discharge or death), and examined by non-opioid drugAcute hospitalization length of stayPain NRS scores: in ED prior to randomization, once admitted in hospital bed, preoperatively in the OR prior to anesthesia, one-hour post operatively, at hospital dischargeTime (hours) to transition to non-opioid analgesiaIncidence of hospital complicationsSafety (Incidence of analgesic complications)

Analgesic complications will be recorded irrespective of the presence or absence of a causal relationship, and include the including:Allergic reactionNausea and vomitingRespiratory depression (hypoxia and hypopnea)HypotensionUrinary retentionConstipation/ileusAbdominal painDizzinessEuphoriaParanoid reactionSomnolenceDeliriumOver-sedation.

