### 2.7. Statistics

Significance is set at an alpha value of 0.05. SAS (Cary, NC) software will be used for statistical analysis. All efficacy analyses will be performed in the intent-to-treat population, defined as all patients who are randomized. Subset analyses will be performed by habitual marijuana use. 

The primary endpoint is the change in morphine equivalents and will be assessed as: post-randomization (48 h after randomization) minus pre-randomization (24 h prior to randomization). No imputation will occur for the primary endpoint. The change in morphine equivalents (mg) will be analyzed with an analysis of covariance (ANCOVA) model to examine the effect of treatment arm, adjusted for age, gender, injury severity score, and clinical characteristics that differ between groups with *p* < 0.15. Of note, our study inclusion criteria allow for patients to present with polytrauma. We anticipate the majority of patients will have injuries to the thorax and extremities, with few patients presenting with severe TBI because administration of opioids and other drugs that alter a neurological assessment tend to be used sparingly. Should there be differences in injury patterns, despite the 1:1 randomization procedure, these differences will be adjusted for in the primary ANCOVA analysis.

Secondary efficacy analyses include the difference between treatment groups in: hospital disposition, hospital complications, and analgesic complications, reported as proportion (%) and analyzed with chi-square tests; morphine equivalents over the hospitalization, hospital length of stay (days), time (h) to transition to non-opioid analgesia, pain NRS scores at all specified time points, reported as median (IQR) and analyzed with a Wilcoxon rank-sum test. Analgesic complications will be described by severity as mild, moderate and severe.

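### The primary endpoint's 24-hour baseline can be only partly observed, because no minimum time in hospital before randomization is set; this adds noise and distorts within-arm reductions but does not bias the comparison of arms

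*Protocol article*

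**What the plan says.** All places are in the Protocol article.

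- **Endpoint (2.7 Statistics).** The change in morphine equivalents is "post-randomization (48 h after randomization) minus pre-randomization (24 h prior to randomization". The baseline term, "pre-randomization (24 h prior to randomization", is the one at issue here. Nothing is imputed for this endpoint. The named ANCOVA covariates are age, gender and injury severity score, plus clinical characteristics that differ between groups at p < 0.15.
- **Window (2.1 Study Design and Setting).** "There is a 48-hour screening/randomization window, a 48-hour treatment window". This is an upper limit only.
- **Timing (2.3 Study Visits).** "The following procedures will be performed at screening, within 48 h of hospital admission". One screening step is to record a 24-hour opioid total. Then: "Once patients are confirmed to meet all criteria and have signed an informed consent, they will be randomized 1:1". No minimum time in hospital is stated.
- **Entry threshold (2.2 Study Subjects).** "Moderately high initial morphine equivalent use ≥50 mg within a 24-hour window during the screening period". The 24 hours bound the time allowed to reach 50 mg. They do not require that 24 hours have passed.

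**The concern.** A baseline of 24 hours before randomization is a full-day quantity only if the patient has been in hospital, with opioid use on record, for those 24 hours. As written, a patient can be eligible, consent and be randomized sooner. Part of the baseline window then falls before arrival, and the recorded total covers only the hours observed.

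Such a patient's change score mixes opioid response with time since arrival. Steady use is scored as an increase, and a real fall can be scored as a smaller fall or a rise. At stake are the precision of the primary analysis and the interpretation of each arm's change from baseline, which is the quantity on which section 2.8 bases the sample size.

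This is a different problem from the unequal lengths of the pre- and post-randomization windows. It would remain if the outcome were put on a 24-hour scale.

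**Working it through.** **1. The plan's own figure.** Section 2.8 gives reductions of 38% and 8% (a difference of 30 points), SD 58, two-sided alpha 0.05 and 80% power. Per arm, n = 2 × (1.96 + 0.84)² × 58² / 30² = 58.7, so 59, or 118 in total. The t-based version gives 60 per arm, 120 in total. With 61 per arm (122 as planned), power is 0.815 by the normal approximation and 0.809 by the t distribution. The plan's figure is reproduced closely enough to serve as the reference.

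**2. How soon 50 mg can be reached.** By the factors in Table 1, 50 mg corresponds to 50 / 3 = 16.7 mg of intravenous morphine or 50 / 0.3 = 167 mcg of intravenous fentanyl, cumulatively. At a constant rate, a patient using 100 mg per 24 h reaches 50 mg at hour 12, and one using 200 mg per 24 h at hour 6.

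**3. Effect on the score.** Let r be true use per 24 h, h the recorded hours before randomization, and d the true proportional reduction. The constant rate is an assumption. The outcome is put on a 24-hour scale to isolate this problem.

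- Recorded baseline = r × min(h, 24) / 24
- Scored change = r(1 - d) - recorded baseline
- Error against the true change = r(1 - h/24) for h < 24, the same in both arms

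For r = 100 mg:

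| Recorded hours | Baseline | No change | 8% fall | 38% fall | Arm difference |
|---|---|---|---|---|---|
| 12 | 50 | +50 | +42 | +12 | 30 |
| 18 | 75 | +25 | +17 | -13 | 30 |
| 24 or more | 100 | 0 | -8 | -38 | 30 |

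As a percentage of the recorded baseline, the 8% and 38% falls become +84% and +24% at 12 hours, and +23% and -17% at 18 hours. If the post value is instead a 48-hour total, unchanged use scores 200 - 50 = +150 mg at 12 hours and 200 - 100 = +100 mg at 24 hours. The part-day baseline still accounts for 50 mg.

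**4. Effect on arm means.** For r = 100 mg, if recorded hours are spread evenly from 12 to 24 (mean 18), both arms shift up by 100 × (1 - 18/24) = 25 mg, to +17 and -13. If randomization is spread evenly over hours 12 to 48, one third of patients have a mean of 18 recorded hours and two thirds have 24. The mean is 22, and the shift is 100 × (1 - 22/24) = 8.3 mg, to +0.3 and -29.7.

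**5. Effect on precision.** Section 2.8 gives no unit for the SD. Read 58 and 30 as percentages of true daily use, and assume that 58 does not already contain this variation and that recorded hours are unrelated to daily use. The added SD is then 100 × SD(h) / 24, where SD(h) = range / √12.

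| Recorded hours, evenly spread | Added SD | Total SD | Power, 61 per arm |
|---|---|---|---|
| 6 to 24 | 21.7 | 61.9 | 0.763 |
| 12 to 24 | 14.4 | 59.8 | 0.792 |
| 18 to 24 | 7.2 | 58.4 | 0.809 |

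Reading 58 and 30 as mg gives the same figures at 100 mg per 24 h. At 200 mg per 24 h, power would be 0.63, 0.73 and 0.79. Those values hold the difference at 30 mg, which is 15% of daily use rather than the planned 30 points, so they are an extreme. At 50 mg per 24 h and a constant rate, the threshold itself takes 24 hours, so the baseline is complete.

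Including patients randomized after 24 hours need not reduce the added variance. Over hours 12 to 48, the variance of min(h, 24) is (1/3)(18² + 12) + (2/3)(24²) - 22² = 12, the same as for 12 to 24.

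**The case against.** **A full day may be intended.** The screening step asks for a 24-hour opioid total, the threshold refers to use "≥50 mg within a 24-hour window during the screening period", and a 48-hour window leaves room for a complete record. The article also condenses a full protocol that may contain a timing rule. This is a fair point, and it makes the matter easy to settle. But none of these sentences says that 24 hours must have elapsed, and section 2.3 makes eligibility and consent the trigger for randomization.

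**Emergency department randomization.** A reader might infer that randomization takes place there. Section 2.6 lists pain scores "in ED prior to randomization, once admitted in hospital bed, preoperatively in the OR prior to anesthesia", and section 2.3 puts the hospital-bed score among the post-randomization procedures. The documents do not support that inference. The first phrase says only that the emergency department score precedes randomization, and section 2.3 has a separate score at randomization. The post-randomization list is no reliable clock either, since it also contains details of marijuana use, although marijuana status is needed beforehand for stratification.

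**Bias between arms.** A reader might also infer that the treatment effect is distorted. It is not. The baseline is fixed before allocation, so its length is balanced between arms on average, and the arm difference in the working is 30 mg at every length. This objection stands in full.

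**Heaviest users.** It is tempting to add that they are worst affected because they reach 50 mg first. That requires randomization to follow promptly on reaching the threshold, which the article does not say.

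**Size.** The share randomized before 24 hours is not given, and the examples rest on a constant rate. This limits what can be said about size, but the gap in the definition remains.

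**Conclusion.** The concern holds in a limited form. As written, the article allows randomization before 24 hours of opioid use have been recorded, and it states no rule for a part-day baseline. Neither baseline morphine equivalents nor observed hours is a named covariate; either could enter only through the p < 0.15 rule.

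The consequence is added variance, and within-arm changes that depend on time since arrival. At an assumed 100 mg per 24 hours, individual scores move up by 25 mg at 18 recorded hours and 50 mg at 12. Arm means move by about 8 to 25 mg in the two scenarios worked. Illustrative power is 0.76 to 0.81 against 0.815, and lower only if daily use is high while the treatment difference stays at 30 mg. The randomized comparison is not biased.

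These sizes assume constant hourly use, evenly spread randomization times and no counting of opioids given before arrival, a point on which the article is silent. Patients randomized at 24 to 48 hours are unaffected.

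**What to change.** **Preferred.** State in sections 2.2 and 2.3 that randomization follows a completed 24-hour in-hospital opioid record. This agrees with the existing screening step and fits within the 48-hour window. It costs one sentence and the loss of patients who are discharged or become ineligible before 24 hours. The documents do not allow that number to be estimated. Randomization would also be confined to hours 24 to 48, so study treatment would start later for some patients; whether that is acceptable is for the investigators to judge.

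**If earlier randomization is kept.** Record for each patient the observed hours within the 24 hours before randomization. Name baseline morphine equivalents and those hours as prespecified ANCOVA covariates in section 2.7. The unadjusted change score is a special case of that model, so apart from two degrees of freedom the fit cannot leave more residual variance. The trial has been recruiting since October 2019, so this is also the remedy for patients already randomized early, provided hospital medication records carry administration times.

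**Not sufficient alone.** Scaling a few hours up to 24 multiplies the noise in the recorded total by 24/h, which is twofold at 12 hours and fourfold at 6. It also overstates the baseline if early use is heavier. For example, a patient given 50 mg in the first 6 hours and 50 mg over the next 18 truly uses 100 mg, but scaling from hour 6 gives 50 × 24/6 = 200 mg.

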### 2.4. Randomization and Blinding

Patients will be assigned to treatment by a randomization schedule developed and maintained by an independent statistician. The randomization allocation sequence was computer generated and is blinded, with allocation hidden until a patient has met all inclusion and exclusion criteria and provided informed consent. Randomization will occur in a 1:1 fashion in blocks of 2 and 4 and stratified by habitual marijuana user (yes/no). 

The assessor, participants, treatment team, and statisticians are unblinded. All assessments are standard and routinely collected by the assessors (ICU and general ward nursing staff), including pain NRS scores and analgesia administration. 

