## 3. Discussion

This is the first randomized trial to investigate whether the addition of dronabinol is effective at reducing opioid consumption for acute pain management of traumatic injury. There are numerous strengths of this study. This clinical trial improves upon our previously published matched cohort study and removes many of the limitations of that study: patients will now be matched by self-reported marijuana use; the pre-treatment period for the controls will be identical to cases rather than being estimated based on the median time from admission to first administration of dronabinol among cases; we will know why controls were not prescribed dronabinol; there are complications and adverse effects that are associated with both systemic analgesics and dronabinol, which will be recorded and analyzed in this trial by treatment arm and by severity. Additional strengths of this study are that it is investigator-initiated and independent from pharmaceutical or other industry interests, and the findings (whether positive or negative) will be submitted to a peer reviewed scientific journal for publication.

Another benefit of this study is the stratified randomization by chronic marijuana usage. Earlier work by the study investigators suggests that pre-injury marijuana use results in increased consumption of opioid analgesics and greater self-reported pain following traumatic injury compared to trauma patients who are marijuana naïve [12]. If the randomized trial demonstrates a greater treatment effect in the subset of chronic marijuana users, this will have wide-ranging clinical implications for acute pain management, because trauma patients have a high prevalence of marijuana use and other substance abuse issues, reported in 40–50% of patients [13,14] that appears to be increasing over time [15]. Thus, if marijuana use significantly affects acute pain management then chronic marijuana users will merit special consideration during acute pain management. 

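### The primary ANCOVA of change in morphine equivalents does not prespecify baseline opioid use or the randomization stratum as covariates, which may cost precision and saves nothing

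*Protocol article*

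**What the plan says.** Section 2.7 (Statistics) defines the primary endpoint as "post-randomization (48 h after randomization) minus pre-randomization (24 h prior to randomization"). The model is an "analysis of covariance (ANCOVA) model to examine the effect of treatment arm, adjusted for age, gender, injury severity score", to which are added "clinical characteristics that differ between groups with" p below 0.15. Differences in injury pattern are also to be adjusted for. Baseline opioid use enters only through the subtraction.

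Section 2.4 randomizes "in blocks of 2 and 4 and stratified by habitual marijuana user (yes/no"). The only role that section 2.7 gives this factor is: "Subset analyses will be performed by habitual marijuana use".

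Both variables are known before randomization. At screening, staff "record 24-hour total morphine equivalents" (section 2.3), and section 2.2 makes at least 50 mg in a 24 h window an entry condition. Marijuana status must be known to assign the stratum. The Discussion (section 3) reports earlier work in which "pre-injury marijuana use results in increased consumption of opioid analgesics and greater self-reported pain".

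**The concern.** A change score fixes the coefficient of baseline at 1. If the true slope of post-treatment use on baseline is not 1, part of the baseline variation stays in the residual, and any chance difference in baseline between arms passes into the estimated treatment effect. Fitting the slope removes both problems.

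The article gives some reason not to expect a slope of exactly 1. Patients are selected on a high recent value, which invites regression to the mean. Section 2.8 also frames the effect as percentage reductions (38% and 8%). If these acted proportionally over windows of equal length, the slopes would be 0.62 and 0.92. If they were reductions in daily rate and the outcome were a 48 h total, the slopes would be 1.24 and 1.84.

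The p < 0.15 rule selects covariates by observed imbalance rather than by prognostic value, so it does not replace prespecification. At stake are the precision of the primary estimate and its protection against an unlucky allocation.

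**Working it through.** **Plan's own figure.** Section 2.8 gives 38% − 8% = 30, SD 58, two-sided alpha 0.05 and 80% power. Per arm, n = 2(1.960 + 0.842)²(58/30)² = 58.7, so 59 per arm and 118 in total (120 with the t distribution). At 61 per arm, power = Φ((30/58)√30.5 − 1.96) = Φ(0.897) = 81.5%. The planned 122 is thus slightly conservative, and it was sized for an unadjusted comparison of two means.

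**Variance with and without baseline.** Let r be the pre/post correlation and k = SD(post)/SD(pre). Neither is in the article, so both are assumed ranges. In units of the baseline variance:
- change score: 1 + k² − 2rk
- with baseline fitted: k²(1 − r²)
- difference: (1 − rk)², which is never negative and is zero only when the slope rk equals 1

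Ratio R = k²(1 − r²)/(1 + k² − 2rk):

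| k | r = 0.3 | r = 0.5 | r = 0.7 |
|---|---|---|---|
| 1 | 0.65 | 0.75 | 0.85 |
| 1.5 | 0.87 | 0.96 | 1.00 |
| 2 | 0.96 | 1.00 | 0.93 |

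k near 2 is plausible if the 48 h figure is a total set against a 24 h baseline; section 2.7 does not say. If k were below 1 the gain would be larger (0.42, 0.47 and 0.49 at k = 0.7).

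**Leak from imbalance.** A baseline difference just missing p < 0.15 is 1.44 × √(2/61) = 0.26 baseline SD. It moves the change-score estimate by (rk − 1) × 0.26 SD. The standard error is √(1 + k² − 2rk) × √(2/61).
- k = 1: 0.85, 0.72 and 0.56 standard errors for r = 0.3, 0.5 and 0.7
- k = 2, r = 0.3: 0.4 × 0.2607/(1.949 × 0.1811) = 0.30 standard errors
- k = 2, r = 0.5: zero
- k = 2, r = 0.7: 0.4 × 0.2607/(1.483 × 0.1811) = 0.39 standard errors, in the opposite direction

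**What the p < 0.15 rule does.** A simulation used 122 patients in two strata (62 and 60), permuted blocks of 2 and 4, k = 1, a stratum shift of 0.5 SD in both pre and post values, age, gender and injury severity omitted, and 4,000 runs per scenario.
- Baseline passed the screen in about 13–15% of trials.
- The stratum passed in none. Incomplete blocks leave at most a two-patient difference within a stratum. The worst case is 32/61 against 30/61 habitual users: z = 0.033/0.0905 = 0.36, p about 0.7.
- Rejection under no effect, for r = 0.3, 0.5 and 0.7: change score alone 5.2%, 5.2%, 4.7%; baseline by the rule 3.6%, 3.7%, 4.1%; both covariates always included 5.2%, 4.9%, 4.7%. Nothing is inflated.
- Variance of the estimate relative to the change score alone, from the simulated standard errors under no effect: by the rule (0.196/0.213)² = 0.85, (0.168/0.182)² = 0.85, (0.134/0.138)² = 0.94; both always included (0.176/0.213)² = 0.68, (0.156/0.182)² = 0.73, (0.129/0.138)² = 0.87. The second set agrees with the k = 1 row above.

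**Power, illustrative only.** Rescaling 58 by √R gives 94.3%, 91.0% and 87.3% at k = 1, and 83.1%, 81.5% and 84.3% at k = 2, against 81.5%. These figures are not predictions for this trial: 30 is in percentage points, 122 is reproduced only if 58 is read so too, and the variance formula is for a change in mg.

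**The case against.** The strongest reply is that this concerns efficiency, not validity. Under randomization the change-score comparison is unbiased, its type I error is nominal, and the sample size already gives the planned power without adjustment on the plan's own inputs. That stands. So does the point that the imbalance rule can let baseline in; the defect is that baseline is not prespecified, not that it is barred.

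A reader might infer more than the documents allow:
- **That the trial wastes 18% to 54% of its patients** (1/0.85 and 1/0.65). That is the k = 1 row alone. With a 48 h total the gain is close to nil, and the article settles neither k nor r.
- **That the change score over-corrects for baseline.** This holds only if rk < 1. At k = 2 it is exact for r = 0.5 and under-corrects for r = 0.7.
- **That omitting the stratum makes the standard error too large.** The Discussion links marijuana use to the level of opioid consumption, not to its change, and an equal shift before and after cancels in a difference. The Introduction's one comparison of change by use within dronabinol patients (−97 against −64 mg, p = 0.41) is too small to settle it either way. The simulation cannot settle it either, because it built in an equal shift.
- **That baseline is the strongest predictor available.** No figure in the article shows this.

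It may also be said that an unseen analysis plan could list these covariates. Section 2.7, however, names the primary model's covariates, so this is a stated choice and not a detail left open.

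**Conclusion.** The point holds as a precision improvement. The fixed covariate list omits two variables known before randomization, and the p < 0.15 rule does not reliably bring either in. Fitting baseline cannot raise the large-sample variance. Over the range r = 0.3 to 0.7 and k = 1 to 2, the residual variance falls by between 0% and 35%. Adjustment also removes a dependence on chance baseline imbalance that, at the edge of the p < 0.15 screen, is worth up to 0.85 standard errors and vanishes when the slope is 1. These sizes rest on assumed r and k and on a linear relation with a common slope. The direction of the variance result does not depend on r or k.

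Most of any gain should come from baseline. The case for the stratum is mainly that the analysis should reflect the randomization. There is a secondary reason: a stratum shift that is equal before and after cancels in the raw change, but once baseline is fitted it reappears as that shift times (1 − slope), so the two belong in the model together.

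**What to change.** Prespecify the primary ANCOVA with treatment arm, pre-randomization 24 h morphine equivalents, habitual marijuana use as randomized, age, gender and injury severity score, all retained whatever the observed imbalance. With baseline in the model, analysing the change or the post-treatment value gives the same treatment estimate.

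The wording should name which baseline is meant: the same 24 h before randomization that is subtracted in the endpoint. Section 2.2 allows any 24 h window during screening for eligibility, and the two may differ. It should also say whether the 48 h figure is a total or a daily rate, because that determines k and hence the likely gain.

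The cost is a change of analysis wording and two degrees of freedom among 122 patients. No new data are needed, and neither the sample size nor alpha changes. The change should be made before the interim test of the primary endpoint described in section 2.9, because section 2.4 states that the statisticians are unblinded.

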### 2.8. Sample Size

The planned enrollment is 122 patients total randomized 1:1 across two study arms: dronabinol or no dronabinol (systemic analgesia only). The sample size is based on a 38% reduction in morphine equivalents with adjunctive dronabinol vs. an 8% reduction in morphine equivalents for systemic analgesics only, with a pooled standard deviation of 58. The analysis was performed using two sample mean tests with normal approximation and equal weights. These estimates were derived via bootstrapping of the final matched study sample of 66 patients. The power to demonstrate the main effect of dronabinol over systemic analgesics is 80% using a 2-tailed alpha of 0.05. 

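### Beyond age, gender and injury severity score, covariates enter the primary ANCOVA only if they differ between arms by chance; followed strictly, this makes the 5% test conservative and gives up precision

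*Protocol article*

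**What the plan says.** The protocol article, section 2.7 (Statistics), analyses the change in morphine equivalents with an ANCOVA for treatment arm. Three covariates are in the model whatever the data show: age, gender and injury severity score. Two further routes depend on the data:

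- The model is also adjusted for "clinical characteristics that differ between groups with" p < 0.15. No candidate list accompanies this.
- If injury patterns turn out to differ between arms, "these differences will be adjusted for in the primary ANCOVA analysis". The text gives neither a threshold nor a definition of injury pattern.

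Section 2.4 states: "The assessor, participants, treatment team, and statisticians are unblinded". It also describes 1:1 randomization in blocks of 2 and 4, stratified by habitual marijuana use (yes/no). Neither that factor nor baseline morphine equivalents is among the three fixed covariates.

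The test level is given in section 2.7: "Significance is set at an alpha value of 0.05".

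**The concern.** In a randomized trial, a baseline difference between arms is chance. A p-value for that difference says nothing about whether the variable predicts opioid use, and prediction is what makes adjustment worthwhile. The rule therefore admits about 15% of the candidates by luck and leaves out strong predictors that happen to be balanced.

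The protocol supplies an example. The Discussion reports that pre-injury marijuana use goes with higher opioid consumption after injury, and randomization is stratified on habitual use. Because stratification balances this factor, the rule will almost never let it into the model. Baseline morphine equivalents has only the same 15% chance as any other candidate.

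Two things are at stake: precision of the primary estimate, and whether the nominal 5% test and its confidence interval have their stated properties. The exact primary model also cannot be known until arm-labelled baseline data have been compared.

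**Working it through.** **Step 1. Reproduce the plan's own figure.** Section 2.8 assumes falls of 38% (dronabinol) and 8% (control), a difference of 30 points. It pairs these "with a pooled standard deviation of 58" and states power that "is 80% using a 2-tailed alpha of 0.05". The unit of the SD is not stated. I take percentage points, because that reading comes close to N = 122; a 70 mg difference (the matched-cohort result in the Introduction) with an SD of 58 mg would need only 11 per arm.

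- n per arm = 2 × (1.96 + 0.842)² × 58² / 30² = 58.7, so 59 per arm (118 in total). The t-test version gives 59.65, so 60 per arm (120).
- With 61 per arm, power = Φ(30/58 × √(61/2) − 1.96) = 81.5% (t-test: 80.9%).

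The stated 80% holds. The calculation uses an unadjusted two-sample test, so it does not depend on the covariate rule.

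**Step 2. What the rule selects.** Each balanced-in-expectation candidate enters with probability 0.15 and is left out with probability 0.85. For independent candidates, the chance that at least one enters is 1 − 0.85^K: 56% for K = 5, 80% for K = 10, 96% for K = 20. Ten candidates give 10 × 0.15 = 1.5 chance entries on average.

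**Step 3. The stratification factor.** Blocks of 2 and 4 hold the arm difference to at most 2 patients per stratum. Take 27 versus 25 habitual users out of 61 (an illustration). The pooled proportion is 52/122 = 0.426, and the standard error is √(0.426 × 0.574 × 2/61) = 0.0895. So z = (2/61)/0.0895 = 0.37 and p is about 0.7. Reaching p < 0.15 (|z| > 1.44) would take a difference of about 1.44 × 0.0895 × 61 = 7.9, roughly 8 patients.

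**Step 4. Why strict use is conservative.** When a prognostic covariate is left out, the reported standard error allows for any chance imbalance in it, yet the rule has already excluded the large imbalances. For a standard normal z restricted to |z| < 1.44, the variance is 1 − 2 × 1.44 × 0.1416/0.85 = 0.52.

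Scale the outcome variance to 1. Assume that the fixed covariates explain 0.05 and the candidates jointly explain R². On average:

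- variance the model reports = 0.95 − 0.15R²
- actual variance ≈ (0.95 − R²) + 0.85R² × 0.52
- type I error ≈ 2Φ(−1.96/√ratio), where ratio = actual/reported

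| R² | reported | actual | ratio | type I error |
|---|---|---|---|---|
| 0.05 | 0.943 | 0.922 | 0.978 | 4.8% |
| 0.10 | 0.935 | 0.894 | 0.956 | 4.5% |
| 0.20 | 0.920 | 0.838 | 0.911 | 4.0% |
| 0.40 | 0.890 | 0.727 | 0.817 | 3.0% |

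**Step 5. Simulation.** Settings: 61 per arm, effect 30/58 = 0.517 SD, three fixed covariates always in the model, and several sets of candidates (up to 10), each admitted if its between-arm t-test gives p < 0.15. The number of candidates and R² are assumptions; the document gives neither.

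| R² of candidates | type I error, rule | power, rule | power, all prespecified |
|---|---|---|---|
| 5–10% | about 4.4–5% | within about 0–3 points of prespecified | – |
| 20% | about 4% | 82–84% | 87–90% |
| 40% | about 3% | 85–86% | 95–97% |

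With the candidates prespecified, type I error is about 5%. The simulated sizes agree with the approximation in step 4.

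**The case against.** The strongest reply is that the plan still meets its own targets. Three sensible covariates are fixed, nothing prespecified is removed, type I error stays at or below 5%, and power stays at or above the planned 80%. The power that is lost is measured against a richer model on which the trial never relied. If the candidates are only modestly prognostic (5–10% of variance), the loss is close to nil. All of this stands, and it limits the severity.

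A second reply is that the candidate list and the definition of injury pattern may sit in an analysis plan that is not shown. That is fair as to the missing details, and their absence is not the point here. The selection rule itself is stated in the article. An analysis plan that listed candidates would still carry the p < 0.15 trigger, and one that dropped it would depart from the protocol.

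A reader might go further and infer that the rule inflates false positives, or that unblinded statisticians pick covariates with the outcomes in view. The document does not support either. Section 2.4 says that they know the arm; it does not say that covariates are chosen after outcomes are examined, and the baseline comparison can be run first. Error above 5% needs someone to choose among models. If an analyst could take the best of the fixed-only, rule-based and all-candidate models, simulated size would be 7.6–8.8%; adding single candidates at will gives 7.7–11.3%. Section 2.7 does not grant that choice. It only leaves room for it through an open list and a trigger without a threshold.

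**Conclusion.** The point holds for the additional covariates only. Selecting them by baseline significance tests is a poorly fixed rule: it omits each prognostic candidate about 85% of the time and in practice shuts out the stratification factor. Followed strictly, it makes the test conservative and wastes precision.

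The size ranges from negligible (candidates explain 5–10% of outcome variance) to a type I error of about 3% and a power loss of roughly 10 points (40%). It rests on assumed values for R² and the number of candidates, on independent, normally distributed covariates, and on the SD of 58 being in percentage points. The document does not show where in this range the trial lies.

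It would be wrong to conclude that the trial is underpowered, that N = 122 must change, or that the whole primary model is data-driven. Severity: should-fix.

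**What to change.** In section 2.7, and in the analysis plan if there is one:

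- Delete the p < 0.15 trigger and the injury-pattern trigger from the primary model.
- Name a short covariate list on prognostic grounds: age, gender, injury severity score, baseline morphine equivalents, habitual marijuana use (the stratification factor) and, if wanted, one injury-region variable with its categories defined.
- Fix this list before any arm-labelled outcome data are analysed, and use the same model at the interim analysis described in section 2.9, so that both looks test the primary endpoint with one model.
- Keep adjustment for observed imbalances as a labelled sensitivity analysis.

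The cost is a wording change and a few degrees of freedom. Adding baseline morphine equivalents and habitual use takes the model from 5 to 7 parameters, so residual degrees of freedom fall from 122 − 5 = 117 to 122 − 7 = 115; an injury-region variable costs one fewer than its number of categories. No extra patients are needed. If the added covariates prove only weakly prognostic, little is gained and little is lost.
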